## Organizations and study population

Beginning February 2014, *Expect With Me* was implemented in five clinical sites in Nashville TN, Detroit MI, and McAllen TX. Each site receives financial and advisory assistance to support the implementation and evaluation process. Yale and UnitedHealth Group recruited clinical sites. An important goal was to include sites located across different regions with different target populations. Interested sites completed a site eligibility form/site profile. If an organization met criteria to participate, a site visit was conducted by the research team to discuss the program procedures and requirements for participation in the study in more detail. The inclusion criteria for health care organizations was as follows: sufficient obstetric patient volume to meet study recruitment goals; support within the institution to integrate group prenatal care into practice; willingness to implement *Expect With Me* according to protocol during the study period; participation in the evaluation study data collection activities; and intention to continue *Expect With Me* after the project period.

To collect organizational data, all clinic staff involved in implementing *Expect With Me* were asked to participate in the process evaluation. To collect extensive data on individual-level outcomes, patients who participate in *Expect With Me* are required to enroll in the evaluation study. We aim to follow more than 1,000 pregnant women through one-year postpartum. Inclusion criteria for patients are as follows: less than 24 weeks pregnant; no severe medical problem requiring individual care only, as determined by the clinical practice; ability to speak English or Spanish; and willingness to participate in the study. Staff at each clinical site explain the study to eligible participants, answer questions, and obtain informed consent. A two-to-one matched cohort of women receiving standard individual care at each clinical site will provide the comparison for the outcome evaluation (two individual care patients for each group care patient). The matched cohort inclusion criteria mirror the study inclusion criteria (e.g., receiving prenatal care at the same clinical practice, entered prenatal care <24 weeks gestation, not transferred out to a high-risk clinic, fluent in English or Spanish, entered prenatal care during the study timeframe). All procedures have been approved by the Yale University Institutional Review Board and Institutional Review Boards at each study site.

## Training and technical assistance

Training for *Expect With Me* is a multi-phase process that targets health system staff at several levels. These phases include: (1) readiness planning and change management; (2) organizational training; (3) facilitator training; and (4) ongoing technical assistance. For several months prior to the start of patient enrollment in *Expect With Me*, health system leadership met regularly with the study team to prepare and build excitement for this care innovation. A series of webinars were conducted and emails sent to prenatal clinic staff providing general overview of *Expect With Me* and the benefits of group prenatal care for practices and patients. A one-day interactive organizational training was held to further familiarize prenatal clinic staff—from front desk staff to medical assistants to nurses, midwives, and obstetricians—with *Expect With Me* and each person’s role in making group prenatal care a thriving part of their practice. This training prepared prenatal clinics to begin *Expect With Me* care*,* including group scheduling, talking to new obstetric patients about group prenatal care, and using the IT platform. Clinical staff who would lead *Expect With Me* groups (e.g., obstetricians, midwives, nurses, medical assistants) participated in a one- to two-day training focused on the development of group facilitation skills. Study staff monitor implementation at each site in real-time through the IT platform and offer technical assistance through regularly scheduled calls to provide ongoing support, share learnings across sites, and troubleshoot issues, as needed. Site visits are conducted to ensure fidelity and support implementation. In-person meetings with all participating sites allow administrators and clinical staff to share knowledge and experience with *Expect With Me*. Group discussions during these meetings provide insights into the implementation process within different clinical settings, and determinants of successful implementation.

## Data collection and measurement

Both quantitative and qualitative data are being obtained at the organizational and patient levels. Table 2 shows how each of the data collection strategies will be used to assess key study outcomes.

**Table 2 Tab2:** Assessment of key study outcomes

Outcome	Definition	Measure	Data Collection Strategy
Outcome evaluation			
Effectiveness	Impact of *Expect With Me* on patient outcomes	Patient-level - Comparison of birth outcomes between *Expect With Me* patients and the matched cohort who received individual care	- Health record reviews - Patient surveys
Process evaluation			
Uptake	Extent to which providers refer patients to *Expect With Me* and deliver group prenatal care sessions	Organization-level - Number and proportion of providers referring patients for *Expect With Me* during the enrollment period - Number and proportion of providers delivering *Expect With Me* group prenatal care sessions	- Health record reviews
	Willingness of eligible patients to participate in *Expect With Me* and extent to which they are representative of the target population	Patient-level - Number and proportion of eligible patients enrolled in *Expect With Me* - Characteristics of *Expect With Me* participants - Reasons patients participate/do not participate	- Health record reviews - Online tracking system - Patient surveys and focus groups
Fidelity	Extent to which *Expect With Me* is implemented as planned	Organization-level - Conformity to the implementation strategy - Conformity to the implementation content - Amount of sessions/groups completed - Amount of content delivered per session - Clinic staff perception about *Expect With Me’s* content and implementation strategy - Satisfaction about implementation within the clinic Patient-level - Amount of sessions attended - Amount of information technology platform use	- Online tracking system - Session evaluations - Provider interviews and focus groups - Patient surveys and focus groups - Site visits
	Amount of the program received by patients		
Sustainability	Impact of *Expect With Me* on healthcare costs	Organization-level - Comparison of financial impact of birth outcomes on healthcare costs - Comparison of utilization of healthcare, including visit attendance, emergency department and neonatal intensive care unit utilization, postpartum long acting reversible contraception uptake, and associated costs - Satisfaction with *Expect With Me* group care and provider training on group care	- Health record reviews - Billing records - Provider focus groups - Provider surveys
	Opinion about *Expect With Me* and the implementation strategy		

### Organizational-level: online tracking system

The *Expect With Me* IT platform was developed to collect real-time program implementation data, including the following information about every *Expect With Me* group: location, facilitators, session dates and times, group composition (e.g., number, gestational age range, and sociodemographic characteristics of participants), and session attendance rates.

### Organizational-level: provider surveys and session evaluations

Group facilitators at each site are asked to complete a questionnaire at baseline and one-year later. Items assessed include provider: demographics, clinical training, previous experience with group care models (baseline only); attitudes about group prenatal care; and perceptions of barriers and facilitators to implementing and sustaining *Expect With Me*. Group facilitators also complete a session evaluation following each prenatal care session scheduled. Data captured by each session evaluation includes: whether or not the session occurred; if a session did not occur, why was it cancelled and the follow-up plan to ensure patients receive their prenatal care; if the session did occur, the topics covered during the group discussion, time spent on physical assessments, and an assessment of the group dynamics and factors that may have influenced attendance or delivery of the session as planned.

### Organizational-level: focus groups and in-depth interviews

Many factors can potentially influence providers’ implementation behaviors including characteristics of the innovation (e.g., complexity, compatibility and alignment with clinic policy, culture, current practices), social setting (e.g., societal norms about prenatal care), organizational context (e.g., support, resources), innovation strategies (e.g., training, reimbursement), patient (e.g., attitudes, adherence to recommended care), and the individual provider (e.g., skills, attitudes) [54, 55]. Focus groups and in-depth qualitative interviews will be conducted with 30–50 key informants (i.e., health care providers, support staff, administrators), until saturation is reached, to identify key factors associated with implementation behavior that can inform strategies to promote adoption, effective delivery, and sustainability of *Expect With Me*. In-depth interviews will last approximately 45 min and focus groups will last approximately 60 min and be audiotaped and transcribed.

### Organizational-level: site visits

During site visits, study team members conduct selective observations of key interactions in prenatal care for patients (e.g., enrollment, group sessions) as well as relevant meetings and other onsite activities. Following each visit, site teams participate in debriefing sessions. Reflections and observations will be synthesized in written form and further examined as part of qualitative data analyses.

### Patient-level: surveys

*Expect With Me* participants complete five surveys: baseline (second trimester), third trimester, birth, 6-months postpartum, and 12-months postpartum. Online survey technology provides standardized measurement, computer-controlled branching through complex questionnaires, automated consistency and range checking, and multilingual administration of questions. Studies with high-risk populations have concluded that computer administered surveys provide valid and more accurate reporting of high-risk behaviors [56–59].

The baseline survey is the most comprehensive and includes patient sociodemographic characteristics and medical history. Follow-up interviews are shorter and assess changes in health-related attitudes and behaviors, as well as prenatal care satisfaction, infant nutrition, and maternal and child health care utilization. Measures include items related to: general health behaviors (e.g., smoking and drinking, diet, physical activity), pregnancy-related attitudes and health (e.g., readiness for labor and care, weight gain and retention), sexual health and risk (e.g., sexual activity, condom use and self-efficacy, intimate partner violence), depression, stress, discrimination, social support, resilience, internet access and use, infant feeding practices (e.g., breastfeeding intention and behavior, introduction of solid foods), and health care system utilization (e.g., emergency room visits, pediatric visits). All of the survey measures were selected from previous research; most have been validated with similar clinical populations [18, 21].

### Patient-level: medical record review

Primary outcomes and other maternal and infant health-related data will be gathered via prenatal, labor and delivery, and postpartum medical record extraction. Record extraction for each patient will be completed after 12-weeks post childbirth and one-year postpartum. Data collected will include medical and reproductive health history, prenatal visit attendance and vital signs (e.g., weight and blood pressure), pregnancy complications and outcomes, delivery information, birth outcomes (e.g., gestational age, birth weight), any neonatal intensive care admission/length of stay, and postpartum healthcare.

### Patient-level: focus groups

Focus groups will be conducted at each site with patients who have delivered their babies. Approximately 40 women will participate. The focus groups will be facilitated by two study team members, last 60–90 min, and be audiotaped and transcribed. Topics covered will include perceptions of prenatal visits, services and support received from the health system, curriculum, IT platform, and impact of the program on family health and well-being.

## Analyses

Descriptive analyses of quantitative data will be performed. Women who participated in group prenatal care and those who received individual care will be matched on the basis of propensity scores. Propensity score matching is a statistical technique to correct for observable difference between the treated and non-treated group, thereby reducing selection bias and strengthening causal inferences, in observational studies [60]. We will use multiple imputation and maximum likelihood techniques to handle missing data and sensitivity analyses to assess the robustness of inferences about treatment effects to various missing data assumptions, as needed.

Generalized linear and logistic regression models will be used to analyze continuous (e.g., gestational age at delivery and birth weight) and dichotomous outcomes (e.g., preterm birth, low birth weight), respectively. Negative binomial regression models will be used to analyze count outcomes (e.g., neonatal intensive care unit days). Each model will include a main effect for treatment group (*Expect With Me* vs. individual care). Because many women who attend group prenatal care sessions also supplement with individual visits [61], adjusted models will control for number of individual visits, as well as contain predictor variables that are clinically meaningful to a specific hypothesis of interest.

Trajectories of change for outcomes that are repeatedly measured over time (e.g., weight) will be examined using linear and non-linear mixed effects modeling, with a random effect for subject. An optimal covariance structure will be selected based on the likelihood ratio test for nested models and based on the Akaike Information Criterion for non-nested models [62]. The main independent effects of time, treatment, and second-degree interactions of these predictors will be considered in each model, adjusting for other covariates as described above.

Multilevel mixed models will be used to identify factors that influence primary outcomes among *Expect With Me* patients, with the effect of site modeled as a random effect. A scale variable that will reflect a woman’s attendance level at prenatal care group visits will be created to evaluate whether there is a “dose–response” intervention effect. Structural equation models will be used to examine factors that may mediate the relationship between participation in group care sessions and improved outcomes.

Focus group and in-depth interview data will be entered into NVivo 10 (QSR International Pty Ltd, Australia) and analyzed using the constant comparative method [63]. This type of thematic analysis is useful for identifying, examining, and reporting patterns within the data [64]. Coding of textual data will occur in iterative steps, in which codes are defined and then refined during review of transcripts from successive interviews and focus groups. Study team members will independently code transcripts. Intercoder reliability will be assessed, joint sessions held to discuss discrepancies, and final codes assigned to observations by a negotiated, group process. We will employ best practices for qualitative research including searching for disconfirming evidence, interviewing multiple respondents at each site for triangulation, and maintaining a detailed audit trail to document analytic decisions [63]. The qualitative data will also be used to interpret and extend the quantitative data findings.

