## Background

Birth outcomes are a nationwide health improvement priority [1]. Nearly four million women in the United States give birth each year, and 84% will give birth in their lifetimes [2, 3]. Despite substantial biomedical advances and intervention efforts, rates of preterm birth (9.6%) and low birthweight (8.1%) in the United States have remained relatively intransigent over the past three decades [4] and are considerably higher than rates in all other developed nations [5]. Extreme racial and ethnic disparities persist in the prevalence of preterm birth and low birthweight as well as consequent infant mortality. Compared to non‐Hispanic White women, Black women are about 50% more likely to deliver preterm and 90% more likely to deliver a low birthweight infant [4]. Infant mortality due to preterm or low birthweight is 3.5 times higher for Black women and nearly two times higher for Puerto Rican women, compared to non-Hispanic White women [6].

The financial and human costs associated with preterm and low birthweight babies are profound. These adverse birth outcomes account for 36% of all US infant deaths [7], and are associated with greater infant and childhood morbidity as well as increased health care costs. Complications of preterm birth include neurodevelopmental disabilities, school and behavioral problems, visual and hearing impairment, cardiovascular and metabolic disorders, and higher risk of preterm in the next generation [8, 9]. Low birthweight is associated with subsequent risk of coronary heart disease, hypertension, and diabetes [10], and has been linked to all-cause mortality among women, and premature death among men [11]. In 2005, the annual economic burden associated with preterm birth in the US exceeded $26 billion [12]. Based on health care inflation from 2005 to 2015 [13], we estimate that these costs now would exceed $38 billion. Employers pay an average of twelve times more for newborn medical care for a preterm birth than for a healthy, full-term baby in the first year of life [14]. Families incur direct medical and non-medical (e.g., special education) costs, as well as indirect costs (e.g., lost productivity). Moreover, preterm birth and low birthweight result in substantial emotional distress for parents who must advocate and make healthcare decisions for fragile newborns [15].

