## Methods/Design

*Expect With Me* is being evaluated via a multisite, longitudinal matched-cohort study, in which data are collected in a real-world settings at the patient and organizational levels. For national scale-up and sustainability, it is essential that the program not only be effective for patients but that the implementation strategy fits with the context of health clinics providing prenatal care [52]. A rigorous multi-method evaluation is being conducted to examine the impact of *Expect With Me* on maternal health and birth outcomes and identify and address barriers to national scalability. Cost analyses are also planned.

The study includes a rigorous process and outcome evaluation. Birth outcomes are the primary study outcomes (e.g., preterm birth, birthweight, neonatal intensive care unit admission/duration). Maternal psychosocial, health behaviors, and health outcomes (e.g., depression, breastfeeding, postpartum weight loss) are secondary outcomes.

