## Cost analyses

The evaluation will include cost analyses [65, 66] comparing *Expect With Me* to individual care, based on patient outcomes (e.g., neonatal intensive care unit admissions and length of stay, emergency department visits). Data from each clinical site’s billing and accounting systems will be used determine patients’ health care charges and actual costs (i.e., amount paid for care collected by the health care facility) including minimum, maximum, median, and interquartile range values of costs for the entire pregnancy through three months postpartum, as well as for the prenatal, childbirth, and postpartum periods separately.

Ordinary least squares (OLS) regressions will be used to test the association between type of care received and maternal and newborn health care costs. Regressions will control for maternal age, race, and other risk factors for adverse birth outcomes. Generalized linear models (GLM) estimates with a gamma distribution and logarithmic link will be used to confirm OLS findings. Alternative approaches to OLS models often are used to account for the long right tail of health care cost distributions. However, OLS results are easier to interpret than many alternative model results. Previous studies of Medicare spending and other health care costs indicated that OLS models perform as well and sometimes better than alternative expenditure models [67, 68].

Costs associated with the provision of group prenatal care from a practice perspective, including start-up and maintenance costs, will also be assessed to inform scalability. Estimates for replication costs will take into account different clinical practice and implementation characteristics.

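### NICU days, listed among the primary outcomes, are analysed as a count that death cuts short, with no stated provision for death

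*Protocol article*

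**What the plan says.** Methods/Design makes NICU use a primary outcome: "Birth outcomes are the primary study outcomes (e.g., preterm birth, birthweight, neonatal intensive care unit admission/duration". Analyses then assigns the duration part to a model: "Negative binomial regression models will be used to analyze count outcomes (e.g., neonatal intensive care unit days". On the content of the models it says "Each model will include a main effect for treatment group", with adjustment for the number of individual visits and clinically relevant predictors. It names no death term, composite, ranking or time-at-risk offset.

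Medical record review lists "any neonatal intensive care admission/length of stay" among the items extracted, together with pregnancy and birth outcomes described in general terms. Infant vital status is not named. Extraction takes place after 12 weeks and at one year. The missing-data sentence, "We will use multiple imputation and maximum likelihood techniques to handle missing data", does not mention death. Cost analyses uses the same NICU quantities: "neonatal intensive care unit admissions and length of stay, emergency department visits".

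Background makes death relevant to these outcomes. Of preterm birth and low birthweight it says "These adverse birth outcomes account for 36% of all US infant deaths". It also treats avoided or shortened NICU stays as a main source of savings, so fewer days are read as better.

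**The concern.** A NICU stay ends in one of two ways, discharge or death, and a count of days does not distinguish them. The infants most likely to die early are mostly the very preterm ones, who would have had the longest stays had they lived. The truncation therefore falls on the part of the distribution that contributes most to the mean.

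If one group had more early deaths, its mean NICU days would fall and the result would lean towards benefit. If group care turned some early deaths into survival with a long stay, those days would count against it. For an outcome called primary and meant to show effectiveness, the scale runs the wrong way for the worst result.

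Two obvious repairs do not work. Dropping infants who died conditions the comparison on survival, which care may affect. Imputing their days treats a stay ended by death as missing data and invents care that never took place.

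**Working it through.** The document gives no NICU admission rate, mean stay, death risk or expected NICU effect, so there is no planned figure to reproduce. The check has three parts.

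**1. How the count scores four infants.** The infants are illustrative. The last column shows one death-inclusive alternative, days alive and out of the NICU to day 90 with death scored 0.

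| Infant | NICU admission | NICU days (fewer reads as better) | Days alive and out of NICU to day 90 (more is better) |
|---|---|---|---|
| Healthy, never admitted | no | 0 | 90 |
| Dies before admission | no | 0 | 0 |
| Dies on day 2 in the NICU | yes | 2 | 0 |
| Very preterm, survives, 80-day stay | yes | 80 | 90 − 80 = 10 |

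On the planned count the second infant ties with the first, and the third looks far better than the fourth. The alternative puts both deaths last.

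**2. Size of the shift from one infant.** The arm size of about 900 comes from Sample size, which expects to follow more than 900 group-care women. Everything else is assumed: 8–12% of infants admitted, mean stay 12–20 days, and an 80-day stay for a very preterm survivor.

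- Mean NICU days per infant = admission share × mean stay: 0.08 × 12 = 0.96, up to 0.12 × 20 = 2.4.
- One such infant dying at once instead of surviving removes 80/900 = 0.089 days from the arm mean: 0.089/2.4 = 3.7% to 0.089/0.96 = 9.3%.
- Three such infants: 3 × 0.089 = 0.267 days, or 11.1% to 27.8%.
- In the comparison cohort of 2,000, one such infant removes 80/2,000 = 0.04 days, or 1.7% to 4.2%.

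**3. The shift against sampling error.** Assume also that the SD of stay among admitted infants is c = 1 to 1.5 times its mean. With admission share p, the relative standard error of the mean over 900 infants is √{[(1 + c²)/p − 1]/900}.

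- p = 0.08: c = 1 gives √(24/900) = 16.3%; c = 1.5 gives √(39.6/900) = 21.0%.
- p = 0.12: c = 1 gives √(15.7/900) = 13.2%; c = 1.5 gives √(26.1/900) = 17.0%.

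The one-infant shift is therefore between 3.7/17.0 = 0.2 and 9.3/16.3 = 0.6 of a standard error. Three infants in the same arm, with no counterpart in the other, give about 0.7 to 1.7.

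**A second illustration of direction.** Let m be mean NICU days per birth from all other infants, d the risk of early death with 0 days, and L the days those infants would use if they lived. If they all survive in one arm and all die at once in the other, the ratio of means is (m + dL)/m. With assumed m = 1.5, d = 0.5% and L = 60, this is (1.5 + 0.3)/1.5 = 1.20. Across m = 0.75–3.0, d = 0.2–1% and L = 30–90 it runs from (3.0 + 0.06)/3.0 = 1.02 to (0.75 + 0.9)/0.75 = 2.2. This all-or-none contrast is extreme. It shows the sign of the distortion and does not forecast its size.

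**The case against.** The strongest reply is that the article is silent on death and states no wrong rule. Nowhere does it say that a death is scored as 0 days, and an article may leave such a derivation to the full protocol or analysis plan. That is fair as far as it goes. However, the article itself chose the variable, called it primary and named the model, and in that form the outcome is truncated by death.

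Other parts of the reply stand and limit the point:

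- **A dead infant scored as healthy.** A reader might infer this. It is exact only for a death with 0 NICU days, and only on NICU use. An infant who dies after admission still counts as admitted. Preterm birth and birthweight are analysed separately and would register most of these infants. The outcome used for sample size, preterm birth, is not truncated by neonatal death.
- **Deaths not collected.** A reader might infer this too. The lists of outcomes and extracted data are given as examples, and the general entries for pregnancy and birth outcomes could hold deaths. The document shows only that death is not named.
- **The cost comparison.** It is tempting to extend the criticism there. An infant who dies early does use fewer NICU days, so raw days are a legitimate measure of resource use.
- **Mechanism.** The study's hypothesis is fewer preterm births. If very preterm births are prevented, deaths and NICU days fall together. The reversal needs an imbalance in early deaths, or would-be deaths that become long-stay survivors, and the document suggests neither. Women who need individual care only, or who transfer to a high-risk clinic, are excluded, so deaths should be few.
- **Size.** All NICU inputs are assumed, and a one-infant shift lies within sampling error.

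**Conclusion.** The point holds as a weakness in one listed primary outcome. As written, NICU duration is a count that death shortens, and no stated provision stops a shorter stay due to death from reading as a better result. The direction follows from the definition and needs no assumption about rates.

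The size is unknown. With 8–12% admitted, a mean stay of 12–20 days and an 80-day survivor stay, one infant moves the mean of an arm of about 900 by roughly 4–9%, or 0.2–0.6 of a standard error. Several such infants on one side would be needed before the comparison was visibly affected. The documents do not support a claim that the evaluation as a whole would mistake deaths for benefit, or that the NICU result will be materially biased. This is a cheap improvement.

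**What to change.** 1. Capture fetal, neonatal and in-hospital infant death, with date, from the records already extracted in both groups, and report deaths by group beside NICU use.
2. For the effectiveness comparison, make the NICU outcome death-inclusive. For the binary part, use NICU admission or perinatal death. For duration, use days alive and out of the NICU to a fixed day, with death scored 0. Day 90 is one possibility. It matches the three-month cost horizon, and the one-year extraction covers it; the first extraction is certain to cover only 12 × 7 = 84 days. An infant still in the NICU on the chosen day would also score 0, so either choose a later day or rank death below that score.
3. Keep raw NICU days, with the negative binomial model, as a resource-use and cost measure.

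The cost is one or two fields in an extraction already under way and a redefined derived variable. The bounded day score also needs a suitable model, such as an ordinal or rank-based one. The downside is that the composite is slightly less direct to read than NICU days.
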